#### Waitlist group (CON)

Participants in the CON group will receive access to four optional weekly health enrichment lectures during weeks 1–4 of the intervention period. These lectures will provide educational material for participants on healthy weight management, diet, mindful meditation, and goal setting. This group will not receive specific information on PA during these lectures. During weeks 5–24, participants will not receive any intervention and will go about their usual activity. After 6 months follow up, CON participants will receive (1) the sleep hygiene education course and (2) PA counseling and a Fitbit® Flex™.

### Intervention compliance and compliance measures

For INT participants, we will track compliance to both the BLT prescription and PA promotion program. Briefly, INT participants will receive monthly calendars monitoring their BLT use, which they will complete and send by mail. Monthly BLT calendars will be reviewed upon receipt from participants and we will follow up with INT participants who do not appear to be following their BLT prescription (i.e., < 50% compliance or did not mail their most recent monthly BLT calendar). We will also monitor weekly PA for each INT participant using the Fitbit online Dashboard, and we will follow up with participants who do not appear to be logging their PA using their Fitbt (i.e., no PA minutes logged on the Fitbit Dashboard within the past 2 weeks). As an additional measure to increase participant compliance and understanding, we will maintain a bi-weekly phone call schedule with participants and will follow up on all missed appointments or missed phone calls.

### Adverse events monitoring

We will have a Data Safety Monitoring Committee ([name], [name], and [name]). All adverse events will be reviewed by the monitoring board. They will stop the study if the adverse event data demonstrate any hazards directly due to the intervention (e.g., increased falls rate) based on monthly report.

### Statistical analyses

The primary objective of this study is to provide evidence for the efficacy of a personalized chronotherapy intervention in improving sleep quality. Our primary analyses will therefore follow the intention-to-treat principle (i.e., all individuals will be analyzed according to their group allocation regardless of compliance). We will evaluate between-group differences (INT vs. CON) in sleep quality using mixed linear models. Maximum likelihood estimation will be used in order to include all randomized participants to estimate treatment effects, regardless of loss to follow up. Time will be considered as a repeated, categorical variable and will be included as a fixed effect in addition to group and group-by-time interaction. The intercept will be specified as a random effect. Primary and secondary outcomes will be analyzed using this same analytic model.

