### Sample size calculation

Our primary outcome measure is sleep efficiency as measured by the MotionWatch8© wrist-worn actigraphy unit (MW8) (CamNtech; Cambridge, UK) [50]. Sleep efficiency is one of several validated objective sleep parameters [51], and it is the gold standard in evaluating insomnia treatment efficiency [52]. Our pilot data suggested that sleep hygiene education alone had a small effect on sleep efficiency after 6 months (*d* = 0.16). As the proposed INT program is multifaceted (i.e., sleep hygiene education + individually timed BLT + individually tailored PA counseling), we anticipate a larger effect size in this RCT. Thus, assuming a two-sided alpha of 0.05, correlation across adjacent time points of 0.88 (estimated from pilot data), 40 participants per group will provide power of 0.85 to detect an effect size of 0.50 at the end of the intervention [53]. To allow for a drop-out rate of 15%, we will recruit a total of 96 older adults (i.e., 48 per group).

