### Measurements

Baseline measurements will be obtained prior to randomization. There will be three measurement sessions: baseline, 12 weeks, and 24 weeks.

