### Treatment allocation

#### Randomization

Participants will be randomly assigned (1:1) to either the INT or the waitlist control group (CON). We will use permuted blocks of varying size to ensure balance over time. To ensure concealment of the treatment allocation, the randomization sequences will be generated and held by a central web-based randomization service.

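### Maximum likelihood is fixed only to keep all randomized participants; REML keeps them too, without standard errors that are about 1% too small

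*Protocol article*

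**What the plan says.** The Statistical analyses section of the protocol article sets out an intention-to-treat analysis by mixed linear models. The fixed effects are time (categorical), group and their interaction, with a random intercept. The same model serves the primary and secondary outcomes. On estimation it says: "Maximum likelihood estimation will be used in order to include all randomized participants to estimate treatment effects, regardless of loss to follow up". It gives no other reason for the choice, such as a plan to compare fixed-effect models by likelihood-ratio tests.

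Three other places supply inputs:
- Sample size calculation sets the error rate, "assuming a two-sided alpha of 0.05", and the sizes: "40 participants per group will provide power of 0.85 to detect an effect size of 0.50 at the end of the intervention" and "To allow for a drop-out rate of 15%, we will recruit a total of 96 older adults".
- Measurements gives the visits: "There will be three measurement sessions: baseline, 12 weeks, and 24 weeks". It also puts baseline before randomization.
- Randomization sets 1:1 allocation.

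**The concern.** The reason given is retention of participants lost to follow-up. That is a property of likelihood-based mixed models in general. REML also uses every observed visit, is valid under the same missing-at-random assumption, and keeps a participant who has only a baseline record. For the stated aim the two estimators are equivalent.

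They differ in the variance estimates. ML divides sums of squares by the number of observations without allowing for the fitted means (here six: two arms by three visits). Its variance components are therefore biased downward in finite samples, and REML makes the allowance. What is at stake is a slight, one-directional understatement of standard errors. Because one model is used throughout, the same mechanism applies to the primary and secondary outcomes alike.

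**Working it through.** **Inputs.** Two-sided alpha is 0.05. There are 40 evaluable participants per group (N = 80) and 48 recruited per group (N = 96). Visits T = 3, allocation 1:1, all from the sections named above. The model is a random intercept with six cell means. The section names no single primary contrast, so the check uses the group-by-time contrast for change from baseline to 24 weeks.

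**The plan's own figures.** The dropout allowance reproduces: 40 / 0.85 = 47.1, and 48 per group gives 96. The power of 0.85 was not reproduced by standard formulas (0.61 comparing 24-week values only, 0.995 for change with r = 0.88, 0.914 for change if the correlation decays to 0.88² = 0.774 over two intervals). The article does not show its formula or the full correlation matrix, so this does not show the figure to be wrong. It has no bearing on the choice of estimator.

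**Step 1: variance ratio with complete data.** The variance of the group-by-time contrast is a multiple of the residual variance.
- ML divisor: N(T − 1) = 2N.
- Unbiased (REML) divisor: (N − 2)(T − 1) = 2N − 4.
- Ratio ML to REML: (N − 2)/N.

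| | N = 80 | N = 96 |
|---|---|---|
| Variance ratio | 78/80 = 0.975 | 94/96 = 0.979 |
| Standard-error ratio k (square root) | 0.9874 | 0.9895 |
| Standard error too small by | 1.3% | 1.0% |

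**Step 2: actual size with a t reference.** With df = 2(N − 2), size = 2 × P(t_df > k × t_crit).

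| | N = 80 | N = 96 |
|---|---|---|
| df | 156 | 188 |
| t_crit | 1.975 | 1.973 |
| k × t_crit | 1.950 | 1.952 |
| Size under ML | 5.29% | 5.24% |
| Size under REML | 5.00% | 5.00% |

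ML therefore adds 0.29 or 0.24 percentage points.

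**Step 3: simulation.** The random-intercept model was simulated with no treatment effect and correlation 0.88 between all visits, 15,000 trials per scenario. Each rejection rate has a Monte Carlo standard error of √(0.05 × 0.95/15,000) = 0.18 points.

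| | N = 80, complete | N = 96, 15% dropout |
|---|---|---|
| Residual variance (true 0.120): ML / REML | 0.117 / 0.120 | 0.117 / 0.120 |
| Group-by-time at 24 weeks, t: ML / REML | 5.49% / 5.21% | 5.11% / 4.89% |
| 24-week difference, t: ML / REML | 5.33% / 5.06% | 5.31% / 5.03% |

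ML rejects 0.2 to 0.3 points more often than REML in these tests, in line with the algebra. For the joint group-by-time F test the gap was 0.4 to 0.5 points (5.70% against 5.28%; 5.55% against 5.09%).

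**Step 4: if the correlation decays.** The article gives 0.88 only for adjacent time points. As an assumption, take first-order autoregressive decay (0.774 between baseline and 24 weeks) with N = 96, 15% dropout and 8,000 trials. The 24-week group-by-time test then rejects 10.4% under ML and 10.0% under REML. The 24-week difference rejects 4.9% and 4.7%. The gap between estimators persists, but it is small beside the effect of the covariance structure.

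**The case against.** The best defense is that the sentence is true. ML does include all randomized participants, and the sentence follows the intention-to-treat statement to explain how dropouts stay in. It does not argue against REML, and the phrase may be loose wording for likelihood-based estimation in general. At 80 to 96 participants in a proof-of-concept trial, the choice could be called a matter of taste.

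Much of this stands. The sentence should not be read as a deliberate surrender of unbiased variances, and the size is minor. But the estimator is a stated choice with a stated reason, not a detail left to another document, and the reason does not distinguish it from REML. If the wording was loose, the same edit removes the ambiguity.

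A reader might also infer a larger inflation, 5.4% to 5.7%. The article does not support that:
- Those figures need a normal reference distribution, and the article names none. A reference distribution and degrees of freedom may properly sit in a fuller document. With a normal reference REML also exceeds 5% (5.15% to 5.36%), so part of the excess is not due to ML.
- The top figure, 5.66%, uses 78 degrees of freedom at N = 80, as an unstructured covariance would. The stated random-intercept model gives 5.48% there.
- All randomized participants enter the analysis, so N = 80 is the less favorable end.

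**Conclusion.** The point holds as a minor, no-cost improvement. The stated reason for ML serves REML equally well. Under the random-intercept model with complete data, ML makes standard errors 1.0% (N = 96) to 1.3% (N = 80) too small and moves a 5% test of the group-by-time contrast to about 5.2% to 5.3% with a t reference. That is unlikely to change a conclusion.

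The result assumes that visits are equally correlated. A reader might infer that the primary test must exceed 5%, or that every outcome's interval must undercover. The article does not establish either, because it names no single primary contrast and gives only the adjacent correlation. Under the decay assumption the 24-week difference shows no inflation with ML, and for the group-by-time test the covariance structure matters far more than the estimator.

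**What to change.** In Statistical analyses, replace maximum likelihood with restricted maximum likelihood, and keep the commitment that all available visits of all randomized participants are used. A small-sample degrees-of-freedom method such as Kenward-Roger is a natural companion, offered as a suggestion because it may already stand in a document not shown.

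The cost is one phrase and a standard software option, with no change to data, visits or sample size. With the reference distribution unchanged, intervals widen by 1/0.9895 − 1 = 1.1% at N = 96 and 1/0.9874 − 1 = 1.3% at N = 80.

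### The mixed model gives each arm its own baseline mean although baseline precedes randomization, so its week-24 treatment contrast is less precise than the same data allow

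*Protocol article*

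**What the plan says.** Four parts of the Protocol article bear on this.

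- **Measurements:** "There will be three measurement sessions: baseline, 12 weeks, and 24 weeks", and "Baseline measurements will be obtained prior to randomization".
- **Statistical analyses:** sleep quality is compared between INT and CON with linear mixed models fitted by maximum likelihood. On the fixed effects: "Time will be considered as a repeated, categorical variable and will be included as a fixed effect in addition to group and group-by-time interaction". The only random effect named is the intercept. The same model serves the primary and all secondary outcomes.
- **Sample size calculation:** the claim is that "40 participants per group will provide power of 0.85 to detect an effect size of 0.50 at the end of the intervention". The inputs behind it are a two-sided alpha of 0.05 and a within-person correlation, given as "correlation across adjacent time points of 0.88 (estimated from pilot data"). Recruitment is then raised to cover losses: "To allow for a drop-out rate of 15%, we will recruit a total of 96 older adults (i.e., 48 per group").
- **Randomization:** "Participants will be randomly assigned (1:1) to either the INT or the waitlist control group (CON").

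The sample size section places the target effect at the end of the intervention, which is week 24. The analysis section does not say which quantity from the model estimates that effect.

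**The concern.** With three sessions and time as a repeated categorical factor, the natural reading is that baseline is one of the modelled outcomes. Group plus group-by-time then gives six free means, including a separate baseline mean for each arm. Because baseline precedes randomization, any difference between those two means is chance. A model that leaves them free spends information on estimating a difference whose expectation is known to be zero.

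The consequence depends on what is read from the model:

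- The difference in change from baseline subtracts the whole chance baseline imbalance. It uses the within-person correlation, but not optimally.
- The plain difference in week-24 means makes no use of baseline, so the high correlation that the sample size section relies on is lost.
- A common baseline mean, or baseline as a covariate, subtracts only the part of the imbalance that baseline predicts. At any correlation below 1 it is more precise than the change contrast, and at any correlation above 0 it is more precise than the raw week-24 comparison.

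At stake is precision that can be had from data already being collected, for the primary outcome and for every secondary outcome given this model.

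**Working it through.** **Inputs from the article.** Two-sided alpha 0.05; n = 40 evaluable per arm; effect d = 0.50; adjacent correlation 0.88; three sessions; 1:1 allocation. The recruitment figure reproduces: 40/0.85 = 47.06, rounded up to 48 per arm, 96 in all.

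**Assumptions.** The 0.50 is taken in units of the SD at a single time point, equal across times. The baseline-to-week-24 correlation, written r, is not stated. Two patterns bracket the working range: first-order autoregressive (AR(1)), r = 0.88² = 0.7744; and compound symmetry, r = 0.88.

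**The plan's 0.85.** Several readings give it.

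- The 2-df group-by-time test, AR(1), with differences of 0, 0.25 and 0.50 at the three sessions. The two changes have variances 0.24 and 0.4512 and covariance 0.2256, so the noncentrality is (40/2) × 0.554 = 11.08. Power is 0.855 by chi-square and 0.841 to 0.848 by F. Under compound symmetry the same test gives 0.988.
- The 1-df change contrast at r = 0.73: variance 2(1 − 0.73) = 0.54, power 0.852.
- The 1-df baseline-adjusted contrast at r = 0.68: variance 1 − 0.4624 = 0.5376, power 0.854.

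Both values of r are compatible with adjacent correlations of 0.88, which require only r ≥ 2(0.88²) − 1 = 0.549.

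**Three week-24 contrasts.** Each has variance (2/n)·v, with noncentrality 0.50/√(2v/40) and power from the noncentral t on 78 df:

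- raw week-24 means: v = 1
- difference in change: v = 2(1 − r)
- common baseline mean or baseline covariate, complete data: v = 1 − r²

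The variance ratio of adjusted to change is (1 − r²)/[2(1 − r)] = (1 + r)/2.

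Raw week-24 means: noncentrality 2.236, power 0.598 whatever r is.

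| Pattern | r | v, change | Power, change | v, adjusted | Power, adjusted | Variance saved |
|---|---|---|---|---|---|---|
| Compound symmetry 0.88 | 0.88 | 0.240 | 0.995 | 0.2256 | 0.996 | 6% |
| AR(1), adjacent 0.88 | 0.7744 | 0.4512 | 0.908 | 0.4003 | 0.937 | 11% |
| AR(1), adjacent 0.80 | 0.64 | 0.720 | 0.740 | 0.5904 | 0.820 | 18% |
| AR(1), adjacent 0.70 | 0.49 | 1.020 | 0.590 | 0.7599 | 0.717 | 25% |

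In the last row the change contrast falls just below even the raw week-24 comparison (0.590 against 0.598). The adjusted contrast does not.

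**The case against.** The strongest reply is that this mixed model is standard, that its group-by-time term carries the treatment effect without bias, and that at the stated correlation the gain over the change contrast is about 3 points of power (0.908 to 0.937) on a figure already above 0.85. A condensed article may also leave the exact contrast to the SAP, which is not shown. Most of this stands. The model is valid, the gain at 0.88 is modest, and not naming the contrast is not by itself a fault. What the reply does not remove is that the fixed effects, as written, leave the baseline means free, and that the better alternative costs nothing.

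Stronger readings are tempting, and the document does not support them.

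- **That the trial has 0.60 power instead of 0.85.** The 0.60 belongs only to a raw comparison of week-24 means. The article does not name that test, it lists the group-by-time interaction as a model term, and a sample size based on within-person correlation points away from it.
- **That 0.85 matches no week-24 contrast.** The correlation over two intervals is unstated, and ordinary 1-df week-24 contrasts give 0.85 at r = 0.73 or 0.68.
- **That power could be as low as 0.21, or that error is inflated to about 8.4%.** The first needs a group effect averaged over all sessions, baseline included. The second needs success to be claimed on either week 12 or week 24, each tested at 0.05. The article proposes neither.

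**Conclusion.** The point holds as one of efficiency. The written model estimates separate baseline means where randomization justifies a common one. Compared with the difference in change, the loss is 11% of variance under AR(1) decay and 6% under compound symmetry at the stated 0.88. It reaches 18% at an adjacent correlation of 0.80 and 25% at 0.70. The lower values matter because the article gives no correlation for the PSQI, the cognitive tests or the other secondary outcomes, and because 0.88 is a pilot estimate.

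The stated power of 0.85 is not shown to be wrong. It cannot be attached to one test, because neither the contrast nor the baseline-to-week-24 correlation is given beside it.

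The figures assume complete data on 40 per arm, an effect scaled to the single-time SD, equal variances, and a fitted covariance that matches the true one. Handling baseline better does not settle the choice of covariance structure, which is a separate matter.

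**What to change.** - Replace the free baseline means with a common one: keep baseline, week 12 and week 24 as outcomes, include time, and allow arm differences only at weeks 12 and 24 (a constrained longitudinal model). Alternatively, use baseline as a covariate with weeks 12 and 24 as the outcomes.
- Take the week-24 INT–CON contrast from that model as the primary test, in line with the end-of-intervention target in the sample size section. Do not use the raw difference in week-24 means as the test.
- Tie the power sentence to that contrast and state the assumed baseline-to-week-24 correlation. At 40 per arm and d = 0.50, power is about 0.94 at r = 0.774 and about 0.996 at r = 0.88; 0.85 corresponds to r of about 0.68.
- Apply the same model to the secondary outcomes.

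The cost is a change of wording in two sections. Sample size, visits and data collection are unaffected. The trial status section reports 38 participants recruited at 1 October 2017, so at that date there was time to settle this before the outcome analysis.

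### The stated random-intercept model sits badly with a planning correlation given only for adjacent visits: if correlation decays, the 24-week change contrast has about 10–11% type I error instead of 5%

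*Protocol article*

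**What the plan says.** In the protocol article, Statistical analyses describes a linear mixed model with group, categorical time and their interaction as fixed effects. Time is called a repeated variable. On covariance it says only this: "The intercept will be specified as a random effect". On estimation: "Maximum likelihood estimation will be used in order to include all randomized participants". The same model serves the secondary outcomes. The section names no residual covariance. It also does not say whether the decisive result is the 24-week change contrast, the 24-week difference in means or the joint interaction test.

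Measurements sets the visits: "There will be three measurement sessions: baseline, 12 weeks, and 24 weeks".

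Sample size calculation is built on "assuming a two-sided alpha of 0.05" and a "correlation across adjacent time points of 0.88 (estimated from pilot data", and concludes that "40 participants per group will provide power of 0.85 to detect an effect size of 0.50 at the end of the intervention". It gives no correlation between baseline and 24 weeks.

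**The concern.** A random intercept with independent residuals implies compound symmetry: baseline to 12 weeks, 12 to 24 weeks, and baseline to 24 weeks all share one correlation. A planning correlation described as applying to adjacent visits is most naturally read as higher than the correlation between visits further apart.

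If so, the model pools three change variances that are not equal. The 24-week change from baseline, which spans the longest interval, is given too small a standard error. The 12-week change is given too large a one. A sponsor who reports the 24-week group-by-time coefficient as the efficacy estimate would then report an interval that is too narrow and a p-value that is too small. The same would happen for any secondary outcome with a similar correlation pattern.

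**Working it through.** **Inputs from the article.** Two-sided alpha 0.05; adjacent correlation 0.88; 40 analysed per group; effect size 0.50; power 0.85; 15% drop-out; 96 recruited; three visits.

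**Assumptions, not in the article.** Equal variances at the three visits (set to 1); independent residuals beside the random intercept; and a baseline-to-24-week correlation, r13, which is varied below.

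**The plan's own figures.**
- Drop-out: 40/(1 − 0.15) = 47.06, rounded up to 48 per group, so 96. This agrees.
- Power: the closest match found is the joint 2-df interaction test with first-order decay (r13 = 0.88² = 0.7744) and an assumed linear divergence of 0, 0.25, 0.50. The noncentrality is 0.50²/(2 × 0.4512/40) = 11.08, where 0.4512 is the 24-week change variance derived below. Power is 0.855 (chi-square) or 0.841 (F).
- The same test with 0.88 between all pairs gives noncentrality 20.83 and power of about 0.985.
- For comparison, the 24-week difference in means alone gives 0.61, and the 24-week change score with r13 = 0.7744 gives 0.91.

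**Variance of the 24-week change under first-order decay.**
- True variance per person: 2(1 − 0.7744) = 0.4512.
- Each adjacent change: 2(1 − 0.88) = 0.24.
- The random-intercept model uses the mean of the three: (0.24 + 0.24 + 0.4512)/3 = 0.3104. Equivalently, it fits a common correlation of (0.88 + 0.88 + 0.7744)/3 = 0.8448.
- At 40 per group, the true SE of the group difference in change is √(2 × 0.4512/40) = 0.150. The model SE is √(2 × 0.3104/40) = 0.125.
- SE ratio: √(0.3104/0.4512) = 0.829, so the SE is 17% too small.
- Type I error: 2[1 − Φ(1.96 × 0.829)] = 10.4%. A nominal 95% interval covers about 90%.
- For the 12-week change: √(0.3104/0.24) = 1.137, giving 2[1 − Φ(1.96 × 1.137)] = 2.6%.

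**Range over the unstated correlation** (adjacent correlations fixed at 0.88; r̄ is the mean of the three; variance ratio = (1 − r̄)/(1 − r13)):

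| r13 | r̄ | Variance ratio | SE ratio | Type I error, 24-week change |
|---|---|---|---|---|
| 0.88 (no decay) | 0.880 | 1.000 | 1.000 | 5.0% |
| 0.84 | 0.867 | 0.833 | 0.913 | 7.4% |
| 0.82 | 0.860 | 0.778 | 0.882 | 8.4% |
| 0.80 | 0.853 | 0.733 | 0.856 | 9.3% |
| 0.7744 (first-order) | 0.845 | 0.688 | 0.829 | 10.4% |
| 0.70 | 0.820 | 0.600 | 0.775 | 12.9% |

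**Simulation check** (100,000 trials, first-order decay, complete data). At 40 per group the 24-week change contrast rejects in 10.3% (REML, t), 10.7% (ML, t) and 11.0% (ML, normal reference). At 48 per group the range is 10.3–10.9%. So ML in place of REML accounts for a few tenths of a point.

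**Other tests from the same fitted model, same truth.** The 24-week difference in means rejects in 5.4–5.6% (ML, normal reference), and the joint 2-df interaction test in 5.7–5.8%.

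**With missing data** (48 per group, 15% monotone drop-out, ML, normal reference). The random-intercept model gives about 12% (3,000 runs) for the 24-week change contrast. An unstructured covariance gives about 6.5% (1,500 runs). The remaining excess reflects ML with a normal reference.

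**The case against.** A reader might infer that the analysis model flatly contradicts the sample size, and that the primary test therefore runs at 10–11%. The article does not support that, for three reasons.

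1. It never states first-order decay or r13. If 0.88 holds for all pairs, the error is 5%.
2. Calling time *repeated* leaves room for a residual covariance that the article does not name and that a statistical analysis plan could supply. The random intercept is the only covariance element stated. It need not be the only one fitted.
3. The decisive contrast is not named, and two of the three natural candidates stay near nominal.

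The power figure does not settle the matter either. It matches decay only when paired with the joint 2-df test and an assumed linear divergence, and that is a test whose error is barely affected. The change-score test under decay gives 0.91, not 0.85.

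All of this stands, and it makes the result conditional. It does not remove the weakness. The random intercept is a positive choice in the article, not a silence. The trial is powered for an effect at the end of the intervention. The model contains a group-by-time term whose 24-week coefficient is an obvious efficacy estimate. The difference in means, at power 0.61, is unlikely to be the planned test. Any decay from 0.88 pushes the error of the change contrast above 5%.

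The preference for REML over ML is secondary, and wanting to keep every randomized participant in the analysis is a sound aim.

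**Conclusion.** The concern holds conditionally. If the residuals are independent, visit variances are equal, adjacent correlations are 0.88 and the deciding result is the group-by-time contrast for 24-week change, type I error is about 10–11% under first-order decay. Across baseline-to-24-week correlations from 0.88 down to 0.70, it runs from 5.0% to 12.9%. Under first-order decay the 12-week change contrast is conservative at 2.6%. If the trial is decided on the 24-week difference in means or on the joint interaction test, the error stays at about 5.4–5.8%, and what remains is a too-narrow interval around the reported 24-week change. This is a worthwhile and inexpensive improvement to the stated model. It does not show that the primary test as written is invalid.

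**What to change.** In Statistical analyses:

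- Replace the random-intercept structure with an unstructured 3×3 covariance over baseline, 12 and 24 weeks, for primary and secondary outcomes.
- Fit it by REML with Kenward–Roger degrees of freedom. REML still uses all available data from every participant, so the reason given for ML is kept.
- Name a fallback, such as heterogeneous AR(1), for use if the model does not converge.
- Name the 24-week contrast that decides the primary outcome.

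The cost is a sentence or two of text and six covariance parameters instead of two. Under first-order decay the 24-week change interval becomes about 21% wider (1/0.829 = 1.206), which is its correct width, and the 12-week interval about 12% narrower (1/1.137 = 0.879). If correlation is in fact constant, little is lost.
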